### Randomisation and allocation concealment

Randomisation takes place at the cluster level, that is, the low-cost public subsidised flats, to avoid contamination. The eight housing projects will be randomised into the intervention arm (4 flats) and control arm (4 flats). The study statistician using a computer generated random number sequence will allocate the low-cost flats into the intervention and control group. The statistician using sealed envelopes will advise the study coordinator of the low-cost flats allocation. Allocation will be concealed from the research team recruiting the flats and participants, as randomisation will only take place after baseline measures have been accomplished.

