### Sample size

The sample size has been estimated for the primary outcome of this study, that is, changes in physical function. The sample size calculation is estimated based on several measures of physical function including mobility, balance, stability (8-Foot Up and Go Test), aerobic endurance (6-minute walk test) and activities of daily living (ADL). In order to achieve 80% power to detect differences in the 8-Foot Up and Go Test, 6-minute walk test and ADL as previously reported [27,64,65], an individually randomised trial would require 45 participants per arm. With a hypothesised intra-cluster correlation coefficient (ICC) of 0.02 and a minimum of 20 participants recruited per cluster, the required sample size is 63 per arm. Assuming 30% loss to follow-up, 82 participants per arm or a minimum total of 164 participants will be required. To recruit at least 164 participants with a cluster size of approximately 21, it will be necessary to recruit 8 low-cost flats.

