### Statistical analysis

The study design provides for four assessments with study participants – at baseline, immediately post-intervention, three months and six months follow-up. Description of participants’ baseline characteristics will be reported by groups. Categorical variables will be summarised by frequencies and percentages. Continuous variables will be summarised by means and SD or non-parametric equivalents. The data analysis for this trial will be undertaken on an intention-to-treat (ITT) principle [66]. The continuous variable outcomes (immediately post-intervention, three months and six months) will be compared between groups using a generalised estimating equations and linear mixed effect models with adjustment for baseline covariates. Groups with dichotomous outcomes will be compared using logistic regression models. Baseline values will be entered as covariates. Statistical significance is set at p < 0.05 and mean 95% confidence intervals (CI) or differences in percentage between the two groups will be reported at the follow-up time points. Data will be entered and analysed with SPSS 22.0 (SPSS Inc., Chicago, IL, USA).

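### The logistic regression named for dichotomous outcomes makes no allowance for the randomised flats, so its standard errors would be too small

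*Protocol article*

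**What the plan says.** The Randomisation and allocation concealment section of the protocol article fixes the unit of randomisation: "Randomisation takes place at the cluster level, that is, the low-cost public subsidised flats, to avoid contamination". Eight flats are split four and four.

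The Sample size section expects residents of one flat to resemble each other. It starts from the statement that "an individually randomised trial would require 45 participants per arm" and inflates this with "a hypothesised intra-cluster correlation coefficient (ICC) of 0.02" and at least 20 participants per flat, giving 63 per arm. It then adds 30% for loss to follow-up to reach 82 per arm.

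The Statistical analysis section assigns GEE and linear mixed models to continuous outcomes. For binary outcomes the method is "Groups with dichotomous outcomes will be compared using logistic regression models", and the only addition is that baseline values enter as covariates. The section names no random effect for flat, robust variance or flat-level comparison for these outcomes. Between-group differences, including differences in percentages, are to be reported at the follow-up time points.

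**The concern.** The sample size pays for clustering, but the analysis named for binary outcomes does not use what was paid for. A logistic regression with baseline covariates takes its variance from the number of residents. With flats randomised, chance differences between flats also enter the arm contrast, and this model leaves them out. Standard errors are then too small, confidence intervals too narrow and p-values too low for any positive ICC.

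The contrast within the section matters. The sentence on continuous outcomes names methods that can carry correlation, whereas the sentence on binary outcomes names one that in its usual form does not. A statistician working from the printed text would have no reason to add the flat. The Discussion says that positive findings are meant to inform health policy, so a false-positive rate well above 5% would have consequences.

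**Working it through.** **Inputs from the article.** ICC 0.02, 20 per flat, 45 per arm before inflation, 63 and 82 per arm after it, and 30% loss (Sample size); 4 flats against 4 (Randomisation and allocation concealment); significance at 0.05 (Statistical analysis).

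**Assumptions.** Two-sided test; flats of equal size; the planning ICC, which was set for physical-function measures, applied to a binary outcome, with 0.01 and 0.05 shown as a range.

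**Step 1: reproduce the plan's figure.** Design effect DE = 1 + (m − 1) × ICC = 1 + 19 × 0.02 = 1.38. Then 45 × 1.38 = 62.1, rounded up to 63 per arm, as stated. Also 63 × 1.3 = 81.9, rounded up to 82, as stated. The plan therefore does use a variance inflation of 1.38.

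**Step 2: completers per flat.** With 20 recruited and 30% lost, 20 × 0.7 = 14. From the total, 82 × 0.7 / 4 = 14.35. So 14 is the planned case and 20 is the case without loss.

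**Step 3: effect of leaving out the flat.** Model SE / true SE = 1/√DE. Actual two-sided type I error = 2 × [1 − Φ(1.96/√DE)].

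- m = 14, ICC 0.02: DE = 1 + 13 × 0.02 = 1.26; SE ratio 1/√1.26 = 0.891; 1.96/√1.26 = 1.746; type I error 0.081.
- m = 20, ICC 0.02: DE = 1.38; SE ratio 1/√1.38 = 0.851; 1.96/√1.38 = 1.668; type I error 0.095.

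**Step 4: simulation and range.** Beta-binomial data were simulated for 4 against 4 flats at one visit, with event rates of 0.2, 0.3 and 0.5 and 200,000 replicates per setting. The test was an unadjusted logistic Wald test that ignores flats.

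| Completers per flat | ICC | DE | SE ratio | Type I error, formula | Type I error, simulated |
|---|---|---|---|---|---|
| 14 | 0.01 | 1.13 | 0.941 | 6.5% | 5.8–6.2% |
| 14 | 0.02 | 1.26 | 0.891 | 8.1% | 7.2–7.7% |
| 14 | 0.05 | 1.65 | 0.778 | 12.7% | 11.7–12.3% |
| 20 | 0.01 | 1.19 | 0.917 | 7.2% | 6.7–7.2% |
| 20 | 0.02 | 1.38 | 0.851 | 9.5% | 9.0–9.4% |
| 20 | 0.05 | 1.95 | 0.716 | 16.0% | 15.5–16.0% |

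The simulation lies slightly below the formula because the Wald test is itself a little conservative here: with ICC 0 it rejects in 4.4–4.9% of runs. A t-test of the flat proportions on 6 degrees of freedom, run on the same data, rejected in 5.1–5.3% of runs.

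**Step 5: price of a valid analysis.** The 97.5% point of t on 6 degrees of freedom is 2.447, against 1.960 for the normal. Interval width relative to the uncorrected one is (2.447/1.960) × √DE: 1.248 × 1.122 = 1.40 at m = 14, and 1.248 × 1.175 = 1.47 at m = 20.

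**The case against.** The strongest reply is that a condensed article may use the term logistic regression loosely for a GEE or mixed logistic model. GEE is named in the sentence before, and the flat is not named as a level for continuous outcomes either. A fuller analysis plan may well say more. That is fair as a guess at intention. It does not rescue the text, because the article does not simply leave the method open. It names one, and that method does not suit the design.

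Second, the size is conditional. The ICC of 0.02 was not set for any binary endpoint, and baseline covariates may lower the residual correlation. This stands. At ICC 0.01 the error by formula is 6.5–7.2%.

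Third, the reach is limited. The Outcomes section defines no dichotomous outcome, and gait speed and grip strength, if analysed as continuous, fall under the other sentence. This also stands. The sentence is not shown to govern any primary comparison.

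A reader might go further in two ways that the article does not support.

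- One might infer that correlation between repeated visits is ignored as well. Nothing says that the three follow-ups are pooled in one logistic model. Differences are to be reported at the time points, which reads naturally as one model per visit, and within-person correlation does not shrink the standard error of such a model.
- One might say that the plan breaches the cluster-trial reporting standard that it cites. The article says that it follows the standard but does not set out its requirements, so this point does not rest on it.

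**Conclusion.** The concern holds for the omitted flat. As worded, the binary analysis disregards the unit of randomisation and is inconsistent with the plan's own sample size. At the planning ICC the standard errors are about 11% (14 completers per flat) to 15% (20 per flat) too small, and a nominal 5% test has a type I error of about 8% to 9.5%. These figures rest on a two-sided test, equal flat sizes and an ICC of 0.02 for the binary outcomes. The direction of the error needs only a positive ICC.

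The point covers whichever outcomes are analysed as dichotomous. It does not show that the primary comparisons are affected, and it makes no claim about pooled visits.

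**What to change.** Replace the sentence on dichotomous outcomes with one of the following, chosen before the outcome data are analysed:

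- a logistic mixed model with a random intercept for flat, or a logistic GEE with flat as the cluster, in either case with a small-sample correction and the arm effect judged on the between-flat degrees of freedom (8 − 2 = 6);
- a flat-level comparison of the eight proportions, by t-test on 6 degrees of freedom or by a permutation test over the 70 possible 4-to-4 allocations. The smallest attainable two-sided p-value of the permutation test is 2/70 = 0.029.

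Add a participant level only if the visits are modelled jointly. Report the differences in percentages with intervals from the same method.

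The change is one of wording; recruitment, conduct and data collection are untouched. The cost in precision is real: intervals about 1.4 to 1.5 times as wide as those of the uncorrected model. The uncorrected intervals claim a precision that a trial of eight clusters does not have.

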### Eligibility screening

Individuals that agree to participate in the study will be requested for their written informed consent and subsequently be screened to see if they fit the inclusion criteria that is aged 60 years and older, residing in low-cost flats in the Klang Valley and living independently at home. The medical history including medications of each participant was interview-administered and recorded as part of the screening process. Exclusion criteria include older people who are already involved or participating in any structured exercise programme, cognitively impaired and having uncontrolled medical condition(s).

The screening will comprise six measurements and physical function tests to identify eligible older adults for the intervention trial. These measurements will include height, walking speed assessment (walking 4 meters unaided), grip strength (Jamar hand dynamometer), body composition analysis using a 4-point bioelectrical impedance analysis (BIA) equipment (TANITA TBF-300A, Tanita, Japan). Tokens in cash and/or kind including rice packs and household items will be given to participants during screening, baseline, intervention and follow-up measurements to encourage and retain participation.

Eligible participants for the CERgAS intervention trial must be willing and able to attend a one-hour session, twice each week for 6 weeks, have a walking speed slower than 1.24 m/s for females or slower than 1.33 m/s for males [48], not suffering from contraindications to exercise including unstable cardiovascular disease, uncontrolled chronic medical conditions, recent fractures and musculoskeletal diseases that would interfere with the safety and conduct of the intervention program. Once individuals have been assessed as being eligible to participate, they will be invited to attend a baseline data collection.

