### Measurements

The following measurements and the physical function tests as aforementioned will be performed at baseline, immediately post-intervention, three and six months at follow-up at a common facility area or hall suitable for exercise sessions at each of the 8 flats.

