#### Anthropometry

Body height will be measured without shoes to the nearest 0.1 cm with a portable stadiometer (SECA 217, Hamburg, Germany). Waist circumference will be measured with a flexible measuring tape (SECA 203, Hamburg, Germany) to the nearest 0.1 cm at the umbilicus, between the tenth rib and the iliac crest. Body composition including fat mass and muscle mass will be assessed through bioelectrical impedance analysis using a portable body composition analyser (TANITA TBF-300A, Tanita, Japan). Resting blood pressure will be also be measured (OMRON HEM-907).

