### Outcomes

#### Primary and secondary outcomes and measurements

The primary outcome of the study is improvement in physical performance among older people assessed by ADL and IADL, grip strength and gait speed. Secondary outcomes will include body composition analysis using BIA along with other measurements consisting of pre-activity readiness for physical activity (PAR-Q+), Physical Activity Scale for the Elderly (PASE), quality of life (SF-12), Falls Efficacy Scale-International (FES-I), fear of falling, depression (GDS), cognitive function (MMSE), nutrition status (MNA) and oral health (GOHAI).

Adverse events will be monitored by the team at the end of each session. Every week participants will fill in a form to indicate if they developed pain, muscle soreness as well as significant injuries or a medical event that results in participant seeking medical attention from a healthcare professional. If participants develop any acute symptoms or any serious adverse events and their condition becomes too serious for the medical doctor in the research team to manage in a community setting, they will be immediately referred and brought to the nearest hospital.

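### Gait speed, grip strength and body composition are each read twice before randomisation, but the analysis names only the baseline reading as a covariate, so some precision already paid for goes unused

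*Protocol article*

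**What the plan says.** All of this is in the Methods of the protocol article.

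- **Eligibility screening** lists what is measured at screening: "These measurements will include height, walking speed assessment (walking 4 meters unaided), grip strength (Jamar hand dynamometer), body composition analysis". The same section makes baseline a later, separate occasion: "Once individuals have been assessed as being eligible to participate, they will be invited to attend a baseline data collection".
- **Measurements** repeats the tests: "The following measurements and the physical function tests as aforementioned will be performed at baseline", and again after the intervention and at three and six months. **Anthropometry** repeats body composition on the same analyser model: "Body composition including fat mass and muscle mass will be assessed through bioelectrical impedance analysis using a portable body composition analyser".
- **Randomisation and allocation concealment** places allocation after both occasions: "randomisation will only take place after baseline measures have been accomplished".
- **Primary and secondary outcomes and measurements** says the primary outcome is "assessed by ADL and IADL, grip strength and gait speed". For body composition it says "Secondary outcomes will include body composition analysis using BIA".
- **Statistical analysis** counts four assessments, the first being baseline, and states "Baseline values will be entered as covariates". Screening values are not mentioned.

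**The concern.** A single reading of a physical test mixes the person's usual level with variation on the day and measurement error. A second reading of the same quantity, taken before allocation, usually predicts follow-up a little better than one reading alone. Here the second reading already exists for everyone who enters the trial, and allocation cannot have influenced it. Leaving it out makes the confidence intervals for gait speed, grip strength and body composition somewhat wider than the collected data require. The trial has four flats per arm and allows for 30% loss, so precision that needs no new participants is worth having.

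**Working it through.** **Are there two usable readings?** Setting the sections side by side: walking speed, grip strength and body composition are taken at screening. People found eligible are then invited to baseline, where the same tests are done again, and the flats are randomised afterwards. Both readings precede allocation, so adjusting for both cannot bias the arm comparison. ADL and IADL are not among the measurements named for screening, so they have one pre-randomisation value.

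**The plan's own figures.** The article gives no figure for the effect of covariate adjustment. Its sample size supplies the number of completers per flat:

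- Design effect: 1 + (20 − 1) × 0.02 = 1.38, and 45 × 1.38 = 62.1, rounded up to 63 per arm.
- Its allowance for loss: 63 × 1.3 = 81.9, that is 82 per arm.
- Completers per flat with 82 recruited, 30% lost and 4 flats per arm: 82 × 0.7 / 4 = 14.35.

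**Assumptions.** Let ρ be the correlation of either pre-randomisation reading with follow-up, and r the correlation between screening and baseline. The documents give neither. I take ρ from 0.5 to 0.8, and r from ρ up to 0.95. Setting r equal to ρ is the favourable end, because it treats screening and baseline as no more alike than either is to a later visit.

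**Residual variance, as a share of outcome variance.**

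- Baseline only: 1 − ρ².
- Both readings: 1 − 2ρ²/(1 + r).

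**Variance of the arm difference if between-flat variance is unchanged.** With an ICC of 0.02 this is proportional to 0.02 + 0.98 × (residual share)/14.35.

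| ρ | r | Baseline only | Both | Fall in residual variance | Fall in arm-difference variance |
|---|---|---|---|---|---|
| 0.5 | 0.5 | 0.750 | 0.667 | 11.1% | 8.0% |
| 0.5 | 0.9 | 0.750 | 0.737 | 1.8% | 1.3% |
| 0.5 | 0.95 | 0.750 | 0.744 | 0.9% | 0.6% |
| 0.6 | 0.6 | 0.640 | 0.550 | 14.1% | 9.6% |
| 0.6 | 0.9 | 0.640 | 0.621 | 3.0% | 2.0% |
| 0.7 | 0.7 | 0.510 | 0.424 | 17.0% | 10.8% |
| 0.7 | 0.9 | 0.510 | 0.484 | 5.1% | 3.2% |
| 0.8 | 0.8 | 0.360 | 0.289 | 19.8% | 10.9% |
| 0.8 | 0.9 | 0.360 | 0.326 | 9.4% | 5.2% |
| 0.8 | 0.95 | 0.360 | 0.344 | 4.6% | 2.5% |

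Worked line for ρ = 0.7, r = 0.9: 1 − 0.49 = 0.510, and 1 − 0.98/1.9 = 0.484. The arm-difference terms are 0.02 + 0.98 × 0.510/14.35 = 0.0548 and 0.02 + 0.98 × 0.484/14.35 = 0.0531. That is a fall of 3.2%, or about 1.6% in the standard error. If between-flat variance shrank in proportion, the arm-difference variance would fall by the full residual-variance percentage.

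**Gait speed.** Entry requires a screening speed below 1.24 m/s (women) or 1.33 m/s (men), so the screening value is truncated. A simulation used one cut-off of 1.28 m/s, assumed means of 0.8 to 1.1 m/s with SD 0.20 to 0.25, and (ρ, r) pairs of (0.6, 0.6), (0.7, 0.7), (0.7, 0.85), (0.7, 0.9) and (0.8, 0.9). The fall in residual variance ran from 4.5% to 16.4%. Truncation reduces the gain but does not remove it.

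**The case against.** The strongest reply is that nothing here is wrong. Adjusting for the baseline value of an outcome is standard practice. The Statistical analysis section does not expressly rule out screening values, and a statistical analysis plan that is not shown could include them. All of that stands. It limits the point to an improvement on the covariates the article names.

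The second reply concerns size. Follow-up comes after a six-week programme and then at three and six months, while the gap between screening and baseline is not stated. If that gap is short, the two early readings will resemble each other more than either resembles follow-up, and the gain shrinks. The Background itself describes gait speed as highly reliable, which points the same way. If screening predicts follow-up only through baseline, a case outside the equal-ρ assumption used here, there is no gain at all. This also stands, and it is why the low values of the range belong in the result.

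Third, a second individual-level reading adds no flats, does nothing for ADL or IADL, and changes no stated power figure: the sample size rests on the 8-Foot Up and Go Test, the 6-minute walk test and ADL. This too is correct.

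What the objections do not remove is that the data are already collected, adjusting for them introduces no bias, and the cost is close to nil.

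**Conclusion.** The point holds as a missed efficiency on gait speed, grip strength and body composition. Under the stated assumptions residual variance falls by about 1% to 20%; at ρ = 0.7 with a screening-baseline correlation of 0.7 to 0.9 it falls by about 5% to 17%. For gait speed truncated by the entry rule, the simulated range is about 4.5% to 16%. The variance of the arm difference falls by about 1% to 11% if between-flat variance is unchanged. All these figures rest on assumed correlations, and the true gain may be near zero if the readings agree very closely.

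A reader might infer three stronger things that the documents do not support:

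- **That the planned comparison is biased or invalid.** It is not: adjustment for baseline alone is valid, and selection on screening speed precedes randomisation.
- **That a gain above 10% can be counted on.** That needs screening and baseline to be hardly more alike than either is to follow-up, which nothing in the article shows.
- **That the change would cure the shortage of clusters.** With eight flats, between-flat variation sets a limit that this covariate may not touch.

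**What to change.** Add to the Statistical analysis section, or to the statistical analysis plan: for gait speed, grip strength and body composition, the screening value and the baseline value are both entered, with separate coefficients, in the model for every follow-up visit; every other outcome is adjusted for its baseline value. Separate coefficients let the data weight the two readings, which suits gait speed because its screening value is truncated by the entry rule.

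Fix this before outcomes are analysed, so that it cannot be a data-driven choice. The Study status section reports screening and baseline as complete with the intervention under way, so the readings are in hand. No new data, visits or participants are needed. The cost is one extra individual-level coefficient in each of these models, for a gain that may turn out small.

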### Study status

Data collection commenced in October 2014 and is on-going. Screening and baseline measurements have been completed and the intervention trial is currently being conducted.

## Discussion

There is an urgent need for locally acceptable sound interventions to promote healthy aging among older Malaysians. The CERgAS trial presents a unique approach, delivering a multicomponent intervention to older adults aged 60 years and older in an Asian urban poor setting. Furthermore, this study is an important step forward and contributes to establishing the effectiveness of a multicomponent exercise and therapeutic lifestyle intervention to increase physical activity and improve nutrition status among community-dwelling older adults. In addition, the demographics of participants who attend the study will be identified and the extent of acceptance towards the intervention according to demographic characteristics such as gender, age and ethnicity will be examined. Moreover, this community-based lifestyle intervention will be conducted in a naturalistic setting, allowing participants to integrate changes into their daily lives in a real-life context. This implies that the intervention delivered can be potentially transferable to other community settings. The process evaluation will provide insight as to how the findings can be extrapolated to urban and rural settings.

While every effort will be made to maximise participation rates in each cluster, this study is limited by the small number of clusters involved in the study and may present as confounding issues during the analyses.

Improved gait speed, muscle strength, quality of life, ADLs and reduced falls accrued from regular participation in exercise and physical activity are anticipated. Adopting a healthy and nutritious diet along with good oral health will likewise improve nutritional status, functional ability and ultimately enhance their quality of life. Finally, the on-going motivational support will provide the elderly adults with the support and encouragement needed to reach their goals, identify barriers and suggest ways to overcome obstacles in efforts to increase their self-efficacy towards healthier aging. To encourage adherence in the intervention, each component (exercise, nutrition and oral care) will be designed to be interactive, enjoyable and manageable.

If the intervention produces significant positive effects, the findings will provide valuable evidence and serve as a model to inform health policies and identify locally acceptable strategies to promote healthy aging and prevent and delay functional decline among older Malaysians.

